#### 2.5.8. The quality and safety monitoring.

The trial’s safety will be monitored once a month by an independent physician with relevant expertise. All participants and visits will be monitored. On the other hand, the auditors will inspect the process several times throughout the period.

#### 2.5.9. Confidential.

All personal information about potential and enrolled participants, as well as proxies, will be kept in a secure location to which no third party will have access.

## 3. Discussion

This study was designed to assess whether glucosyl hesperidin has a positive effect on hepatic function in patients with PBC. Patients with PBC, who are mostly middle-aged and older women, have a relatively high prevalence of comorbidities and are generally prone to high oxidative stress conditions. In addition, previous studies have shown that antioxidant activity via the Nrf2/Keap1 pathway is more severely impaired with the exacerbation of liver pathology in patients with PBC.^[8]^ Furthermore, it has recently been reported that S-adenosyl-L-methionine, which is associated with redox regulation, protects against mitochondria-derived oxidative stress by upregulating the expression of Nrf2 and its target gene, HMOX-1, in human cholangiocytes.^[24]^ Thus, the Nrf2/Keap1 pathway is generally impaired in chronic liver diseases, including PBC, and attempts to inhibit the pathological progression of chronic liver diseases by activating this pathway are easily understood. UDCA, the first-line drug for PBC, has the ability to activate the Nrf2/Keap1 pathway. However, because enterohepatic circulation is required for its efficacy, UDCA’s pharmacological effect naturally diminishes as intrahepatic biliary stasis progresses. Therefore, new drug candidates for the treatment of PBC must include ingredients that are safe to use in combination with UDCA in terms of duration and dosage. In this regard, glucosyl hesperidin has been chosen as the target component of this medical intervention study, and a new treatment regimen combining UDCA, the standard treatment for PBC, with glucosyl hesperidin has been proposed, with a randomized clinical trial to confirm its efficacy. Glucosyl hesperidin is a common natural component derived from citrus plants that acts as a safe and effective Nrf2/Keap1 pathway activator.^[25]^ The concept of using an existing chemical substance with established safety for oral intake to improve the condition of a designated intractable disease whose pathology is not fully understood is novel and will contribute to the development of a new treatment option. If this study shows that glucosyl hesperidin has a dose-dependent effect on lowering serum biliary enzyme levels, it would be very significant because it would mean that intrahepatic microcholangitis in patients with PBC is being treated, and thus may contribute to the suppression of liver fibrosis progression in a physically safe manner. Furthermore, if the medical efficacy of glucosyl hesperidin in patients with PBC is confirmed, the impact of these study’s findings will be enormous, as it may lead to improvements in the pathogenesis of numerous other inflammatory diseases in which disruption of the antioxidant stress mechanism is a major etiological factor. In this study, case enrollment began in the summer of 2022, with results expected in 2024.

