## 2. Methods

### 2.1. Design

This is a multicenter, open-label, randomized, parallel-group study comparing the influence of glucosyl hesperidin on liver function with UDCA treatment in patients with PBC (Fig. 1). Patients aged 20 years or older are eligible to participate. The inclusion and exclusion criteria are listed in Table 1. Patients will be randomly assigned to either the 500 mg/day or 1000 mg/day treatment groups. In these treatment groups, either 500 mg or 1000 mg of glucosyl hesperidin will be given orally once per day for 24 weeks in addition to ongoing UDCA treatment.

**Table 1 T1:** Inclusion and exclusion criteria.

Inclusion criteria
1.Primary biliary cholangitis.
2.Be at least 20 years old at the time of consent acquisition.
3.Patients with a performance status ECOG of 0 or 1.
4.Patients with no dose changes for UDCA and fibrate.
5.Patients who were adequately informed about the study’s objectives and voluntarily provided written consent by themselves or their surrogate.
Exclusion criteria
1.Patients with hesperidin hypersensitivity.
2.Patients who routinely consume hesperidin-containing health foods prior to participating in this study.
3.Patients scheduled for or undergoing treatment for malignant tumors.
4.Patients with a NYHA functional classification of 2 or higher.
5.Patients who experience dyspnea during daily exertion.
6.Patients with a total bilirubin level of 3.0 mg/dL or higher, or a Child-Pugh classification of B or C.
7.Patients with an eGFR of less than 30 mL/minute/1.73 m^2^.
8.Patients who are or may become pregnant.
9.Patients who participated in other clinical trials within 3 months before starting hesperidin administration.
10.Patients deemed unsuitable by doctors to participate as research subjects.

ECOG = Eastern cooperative oncology group, eGFR = estimated glomerular filtration rate, NYHA = New York heart association, UDCA = ursodeoxycholic acid.

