#### 2.5.2. Primary endpoint.

The average “rate of change of biliary enzyme levels (serum GGT levels) at 24 weeks after glucosyl hesperidin administration from before administration (0 weeks)” will be compared between groups using an unpaired Student’s *t* test. In addition, the point estimate of the difference between the groups and the 95% confidence interval will be calculated.

The rate of change will be calculated as follows: serum GGT level (24 weeks)-serum GGT level (0 weeks)/serum GGT level (0 weeks).

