#### 2.5.3. Secondary endpoint.

For each item, the mean values for each group will be compared between groups using an unpaired Student’s *t* test. In addition, the point estimate of the difference between the groups and the 95% confidence interval will be calculated. The rate of change will be calculated as follows: each evaluation item (at each evaluation point other than 0 weeks) – each evaluation item (0 weeks)/each evaluation item (0 weeks). The following items will be included: Rate of change in biliary enzyme levels (serum GGT level) after glucosyl hesperidin administration (8 and 16 weeks) from before administration (0 weeks); rate of change in hepatobiliary enzyme levels (serum alkaline phosphatase, transaminase, and total bilirubin levels) after glucosyl hesperidin administration (8, 16, and 24 weeks) from before administration (0 weeks); and rate of change in Nrf2 protein expression levels and its target gene (HMOX-1) after glucosyl hesperidin administration (8, 16, and 24 weeks) from before administration (0 weeks).

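### The trial is said to confirm efficacy, but both arms receive glucosyl hesperidin and every listed test compares 500 mg with 1000 mg, so it can test only dose dependence

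*Protocol article*

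**What the plan says.** **Aim.** The Discussion opens with "This study was designed to assess whether glucosyl hesperidin has a positive effect on hepatic function" in patients with PBC. It later says that the combination with UDCA "has been proposed, with a randomized clinical trial to confirm its efficacy". The abstract's Discussion paragraph likewise gives the aim as assessing a supportive effect in patients already on UDCA.

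**Design.** Section 2.1 describes the study as "comparing the influence of glucosyl hesperidin on liver function with UDCA treatment in patients with PBC". It then states "Patients will be randomly assigned to either the 500 mg/day or 1000 mg/day treatment groups", and that "either 500 mg or 1000 mg of glucosyl hesperidin will be given orally once per day for 24 weeks in addition to ongoing UDCA treatment". No arm goes without glucosyl hesperidin.

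**Sample size.** Section 2.4 powers the trial for the difference between the standard-dose and high-dose groups.

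**Analysis.** For the primary endpoint (section 2.5.2), the mean rate of change in GGT at week 24 "will be compared between groups using an unpaired" t test. For the secondary endpoints (section 2.5.3), "the mean values for each group will be compared between groups using an unpaired" t test, and section 2.5.4 uses the same method for the exploratory ones. No test within an arm against baseline is specified.

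**Time points.** The secondary enzyme and Nrf2 endpoints are measured "after glucosyl hesperidin administration (8, 16, and 24 weeks) from before administration (0 weeks"). The exploratory endpoints also stop at week 24. Table 2 schedules one more blood examination at week 36.

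**The concern.** The stated aim asks whether glucosyl hesperidin helps patients on UDCA. The randomized contrast asks whether 1000 mg differs from 500 mg. The two questions have the same answer only under some dose-response shapes.

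What is at stake is the reading of the primary result. If the difference is not significant, the trial has not answered its stated question in either direction. What then remains is the change from baseline within each arm. In an open-label trial without a hesperidin-free arm, that change cannot be separated from time trends, background therapy or altered behaviour. The abstract describes the endpoints as before-and-after changes, and the Discussion looks ahead to efficacy being confirmed. The plan should therefore say beforehand what each result may be taken to show.

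**Working it through.** **1. The plan's own power figure.** Inputs from section 2.4: dose difference 5%, two-sided significance level 5%, power 90%, about 110 enrolled and 100 evaluable. Figure 1 allocates 55 per arm, so 50 per arm are taken as evaluable. Section 2.4 prints a standard deviation (SD) of 5% and also a figure of 7.5% labelled a probability. Both are tried as the SD.

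Standard error of the difference = SD × √(2/50) = SD × 0.2. Power ≈ Φ(difference / standard error − 1.96).

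- SD 7.5%: standard error 1.5, 5/1.5 = 3.33, power = Φ(1.37) = 91.5% (91.0% with the noncentral t). The required size is 48 to 49 per arm.
- SD 5%: standard error 1.0, 5/1.0 = 5, power = Φ(3.04) = 99.9%. The required size is 22 to 23 per arm.

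The 90% is reproduced only with 7.5% as the SD. That labelling problem is a separate matter. What counts here is that the 90% is power to detect a 5-point difference *between doses*. No power can be calculated against UDCA alone, because the trial has no such contrast.

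**2. Effect common to both doses.** Let b be the mean change that would occur on UDCA alone, and e₅₀₀ and e₁₀₀₀ the effects added by each dose. The primary contrast estimates (b + e₁₀₀₀) − (b + e₅₀₀) = e₁₀₀₀ − e₅₀₀. The term b cancels, so neither e₅₀₀ nor e₁₀₀₀ can be recovered. If e₅₀₀ = e₁₀₀₀, the expected difference is 0 and the test is significant 5% of the time, whether the shared effect is nil or large.

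**3. Smaller dose differences.** These true differences are assumed for illustration (50 per arm, two-sided 5%, noncentral t).

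| True dose difference | Power, SD 5% | Power, SD 7.5% |
|---|---|---|
| 0 | 5% | 5% |
| 1 point | 17% | 10% |
| 2.5 points | 70% | 38% |
| 5 points | 99.9% | 91% |

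**4. Linear dose response (assumed).** If the effect is proportional to dose, e₅₀₀ = e₁₀₀₀/2 and the contrast is e₁₀₀₀/2. A 5-point dose difference then needs a 10-point effect of 1000 mg over no hesperidin. A 5-point effect of 1000 mg gives a 2.5-point contrast, with 38% to 70% power. The contrast is informative in this case, but it sees only half of the effect.

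**5. Week 36.** Table 2 places this blood test nominally 36 − 24 = 12 weeks after treatment ends. With windows of ±2 weeks at week 24 and ±4 weeks at week 36, the interval runs from 12 − 6 = 6 to 12 + 6 = 18 weeks. It appears in no listed efficacy endpoint. Table 2 does not say which analytes are measured then.

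**The case against.** **The trial is not silent on efficacy.** A reader might infer that a dose comparison can say nothing about whether the product works. The documents do not support that. The Discussion gives its own route, which is to show a dose-dependent fall in biliary enzymes. A significant randomized advantage of 1000 mg would be evidence of a drug effect, provided that the effect does not reverse with dose. This stands, and it limits the point to what the design cannot deliver.

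**The two-dose design is openly stated.** The abstract, section 2.1 and section 2.4 all say that two doses are compared, and another dose is a legitimate randomized comparator. The word control in the title is therefore not clearly wrong. The design sentence in section 2.1 may also mean the influence of the product during UDCA treatment. Both readings are fair. They do not rescue the efficacy sentence, which claims more than this comparator can support.

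**Week-36 blood is not thrown away.** A reader might infer that it is, because no efficacy endpoint uses it. Table 2 also ticks adverse events at week 36, section 2.3 counts abnormal laboratory results as adverse events, and section 2.5.6 calculates incidence over the observation period. The sample can therefore feed safety reporting. Nor would a week 24 to 36 change supply the missing comparator: it is as uncontrolled as the change from week 0 to 24.

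**No within-arm claim is planned.** A reader might infer that a fall within an arm will be presented as efficacy. The listed analyses contain no such test, so this is a risk to guard against, not a stated intention.

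**The article is condensed.** A fuller protocol or analysis plan may add supportive analyses. It cannot create a hesperidin-free contrast from the two arms described.

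**Conclusion.** The stated aim goes beyond the design, and the aim and conclusion wording should be corrected before analysis. The planned tests are directed at a dose difference. They cannot estimate benefit over UDCA alone, cannot show that 500 mg works, and cannot detect an effect common to both doses. For a shared effect of any size the chance of a significant primary result is 5%, so a null result does not distinguish two equally effective doses from two ineffective ones. The 5% holds for any equal true effect, given the usual t test conditions. The other power values rest on 50 evaluable patients per arm, an SD of 5% to 7.5%, and dose differences assumed for illustration. Reading a significant advantage of 1000 mg as evidence of a drug effect rests on the assumption that the effect does not reverse with dose.

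**What to change.** 1. Restate the objective as a test of dose dependence: whether the relative change in GGT at week 24 differs between the 1000 mg and 500 mg groups, both on ongoing UDCA.
2. Add a conclusion rule. A significant advantage of 1000 mg supports a dose-dependent drug effect but does not give the size of benefit over UDCA alone. A non-significant difference is evidence neither for nor against efficacy. Change from baseline within an arm is descriptive only.
3. Replace the Discussion's efficacy sentence with wording limited to dose dependence, and align the Discussion's opening sentence and the abstract. The title's reference to control may stay if the text makes clear that the comparator is another dose.
4. Optional and supportive only: if GGT and alkaline phosphatase are measured at week 36, report the week 24 to 36 change by dose group with 95% confidence intervals. Label it an uncontrolled before-after comparison and not confirmation of efficacy.

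The cost is a wording amendment and, if item 4 is taken up, one descriptive table. No arm, visit or patient is added. The price is a more modest claim. Enrolment has begun, so the change should be made and dated before the data are fixed for analysis.
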